## Abstract

**Background:**

Stroke is a leading cause of death and disability worldwide. Although survival rates from mild-to-moderate stroke are high, long-term functional impairment remains common, requiring sustained self-management beyond traditional rehabilitation. Conventional models depend on institutional medical care, which not only drives up costs but also disrupts continuity of care. Meanwhile, psychological, risk-related, and behavioral factors are often overlooked. Advances in artificial intelligence (AI) and mobile health provide opportunities for individualized, long-term support. Based on this, we developed the AI Health Education Accurately Linking System (AI-HEALS) to evaluate its potential to improve physiological parameters, risk perception, and self-management in patients with mild-to-moderate stroke.

**Methods:**

This single-blind randomized controlled trial evaluates AI-HEALS, delivered via WeChat (China’s most widely used social media app), to improve the monitoring of key physiological indicators in patients with mild-to-moderate stroke. Eligible participants are randomly allocated either standard care as a control or standard care plus a three-month regimen of AI-HEALS. It features an AI-powered interactive Q&A system that supports both voice and text communication, real-time monitoring of physiological and behavioral indicators, personalized health reminders, and specially designed educational content. These are all offered through the official WeChat account “Stroke Health Management Expert.” The primary outcomes are changes in blood pressure, glucose, and blood lipids. Secondary outcomes include risk perception of recurrence of stroke, self-management behaviors, and psychological state of mind. Follow-up assessments are conducted at 3, 6, and 9 months after completion of the intervention to evaluate both short-term and sustained effects.

**Discussion:**

This protocol presents a new AI-mHealth approach to delivering stroke care. If proven feasible and effective, AI-HEALS could offer a scalable and sustainable model for improving long-term health outcomes, reducing the risk of recurrence, and optimizing the use of healthcare resources for stroke and other chronic conditions.

**Clinical trial registration:**

https://www.chictr.org.cn/showproj.html?proj=251515, Identifier, ChiCTR2500096422.

## Introduction

1

Stroke is one of the leading causes of death as well as disability on a worldwide basis, endangering human health severely (1). According to the Global Burden of Disease Study 2019, stroke accounted for approximately 6.55 million deaths worldwide, with 101 million people living with the condition and a total of 143 million disability-adjusted life years (DALYs) lost (2). The incidence of stroke rises sharply with population aging, a trend that is particularly pronounced in China (3). Stroke has both a high incidence as well as deep impact on patients’ lives of daily living as well as occupational functioning (4). Speech dysfunction, movement, and cognition, are easily affected by stroke, causing evident quality of life decrement (4, 5). Moreover, stroke puts a tremendous economic burden on patients’ families, as long-term care and rehabilitation requires them financially for years at a stretch (2, 6). Caregivers themselves may develop psychological disturbance and physical disorders (7, 8). Medical expenses and societal expenses of stroke are enormous (6). According to the American Heart Association, stroke imposes a substantial economic burden on the United States health system, costing approximately $34 billion each year (9). As population aging keeps accelerating, incidence of stroke as well as related burdens keep rising (10).

Current standard rehabilitation for patients with mild-to-moderate stroke typically includes physical therapy, occupational therapy, speech therapy, and structured health education (11, 12). These approaches mainly target the restoration of physical functioning, improvement in activities of daily living, and facilitation of community reintegration. These are primarily focused on assisting and supporting patients in restoring their physical functions and helping them to return to society. Additionally, new concepts, such as virtual reality therapy and therapy assisted by robots, are adding new dimensions to the available options for patients (13), while there are some limitations to the present model. First, traditional rehabilitation generally requires patients to attend specialized facilities in person. This requirement can impose substantial financial and logistical burdens, particularly with respect to travel, time commitments, and repeated appointments (14). These difficulties tend to limit the frequency and ease of rehabilitation, which are important for optimal recovery. Second, the standard approaches to rehabilitation are primarily physical and do not emphasize psychological well-being, the perception of risk, and behavioral shifts as much. However, psychological distress, lack of confidence, and ineffective behavior shifts are well-established poor predictors of secondary prevention and the quality of life for survivors of stroke (15). The standard care does not contain inherent components that address such aspects. Finally, while technology-assisted or remotely delivered rehabilitation, such as videoconferencing-based assessments and home-based telerehabilitation, has shown promising functional and neural outcomes (16, 17), these approaches remain primarily oriented toward motor recovery rather than comprehensive self-management support. They often do not receive continuous health education, behavioral support, and combined tracking of health and lifestyle factors. As such, despite advanced technology, the present care model fails to comprehensively address the needs for managing patients with mild to moderate stroke.

Mobile health (mHealth) and artificial intelligence (AI) technologies have simplified personalized and continuous support for people living with chronic conditions. mHealth applications provide distant access to health information, reminders, and patient self-check facilities. AI can improve such applications by allowing for response generation, tailored content, and proper use of patient-submitted information. These concepts assist patients to stay engaged and simplify their overall self-management. For the purpose, the Artificial Intelligence Health Education Accurately Linking System (AI-HEALS) was designed as a WeChat-based tool for complementing the conventional rehabilitation process for patients with mild to moderate stroke. AI-HEALS incorporates proven behavioral model concepts, the Health Action Process Approach (HAPA) and the Multi-Theory Model (MTM) (18, 19), to direct the design of the education and behavioral components. AI-HEALS consists of the following functional elements: an AI-supported question-and-answer section with an organized and updated knowledge base, the capacity for the recording of healthcare and behavioral information, reminders, and health education. Though named AI-HEALS, the system actually serves as an AI-driven health education and management system and not as therapy. This tool would assist patients in managing their health outside the healthcare environment.

Based on it, this protocol describes a single-blind, randomized controlled trial (RCT) designed to systematically evaluate the effectiveness of the AI-HEALS in promoting self-health management among patients with mild to moderate stroke. The specific objectives of the study are:

To determine whether a 3-month AI-HEALS–based comprehensive intervention improves physiological indicators, including blood pressure, blood glucose, and body weight;To assess the intervention’s impact on psychological outcomes, such as anxiety, depression, and self-efficacy;To evaluate the effectiveness of the intervention in enhancing self-management behaviors, including medication adherence, engagement in rehabilitation exercises, and healthy dietary practices.

## Methods

2

### Study design

2.1

The research design of our study will be a single-center, randomized, single-blind, parallel-group clinical trial. The subjects of the study will be patients with mild to moderate stroke from the public general hospital of Luoyang, China. Figure 1 shows the complete workflow of the study as well as group allocation procedures.

**Figure 1 fig1:**
[figure not shown]
Flow chart of patient recruitment and study implementation.

### Randomization and blinding

2.2

Single-blinding will be applied for the study, because the AI-HEALS intervention would not be possible for the participants and the intervention team to be blinded regarding the allocation of the groups. In the context, single-blinding indicates that the people involved in the evaluation process and analysis are blinded to the allocation groups of the participants during the evaluation and data analyses. For the randomization process, it would implement the use of the computer-generated random number sequence. For allocation, it would use the 1:1 allocation ratio. An independent team member who is not involved in participant recruitment, clinical care, or intervention delivery will generate the randomization sequence and manage allocation concealment. Group assignments will be released to the intervention team only after allocation is complete to ensure that recruitment personnel remain blind to group assignment at the time of enrollment. For avoiding sharing between allocation groups, the participants would be admitted to separate units according to their allocation (Ward A for the intervention and Ward B for the control groups). Although participants and care providers cannot be blinded, several measures will be implemented to reduce performance and detection bias:

Outcome data will be collected by research assistants who are blinded to group allocation.Data analysis will be performed by statisticians who are blinded to group identities, with datasets fully de-identified prior to analysis.Randomization and allocation procedures will be managed by an independent researcher not involved in recruitment or intervention provision.Physical separation of inpatient units will minimize interaction between participants from different groups.

All data will remain securely stored and de-identified to maintain the integrity of the blinding process.

### Study sample

2.3

Consecutive sampling method will enroll stroke patients currently receiving treatment at a tertiary Grade A hospital of Luoyang, China, from February 2025 to February 2026. Inclusion and exclusion criteria are set as follows:

Inclusion Criteria: Patients 18 to 60 years old; Diagnosed as acute stroke based on 2019 Chinese major cerebrovascular disease diagnostic guidelines (20), with confirmation of stroke lesion by cranial CT or MRI; A score of ≤5 on the National Institutes of Health Stroke Scale (NIHSS) at the time of admission (21, 22); Patients gave their informed consent and voluntarily participated in this study.

Exclusion Criteria: Those with severe mental illness or cognitive impairment who are unable to cooperate with the researcher; those who are unable to use a smartphone; and those who have participated in related research in the past.

Withdrawal Criteria: Voluntary drop-out of the participant due to personal reasons (e.g., scheduling, loss of interest); During the research, seriousness of severe adverse events, such as severe illness or acute illness episode (e.g., myocardial infarction, serious infection), that requires the cessation of the intervention; Clinical changes or new guidelines for treatment that would necessitate alterations to the participant’s treatment regimen that may conflict with the study intervention.

### Sample size

2.4

This research study was designed as a single-blind RCT. The primary objective of the study was to ensure if the AI-HEALS intervention program is feasible, acceptable, and easily implementable, as opposed to determining the efficacy of the program. Thus, it is sample size was determined based on the format for conducting a pilot study as proposed by Billingham et al. (23). Based on such recommendations, the minimum number of participants for our study would be 50, consisting of 25 per group, to ensure the objectives are achieved for the pilot study. Taking into consideration the expected dropout of 20%, the minimum number of people to recruit would be 60, 30 for each group. This sample size is expected to provide reliable estimates of feasibility parameters and preliminary effect size estimates for planning a subsequent fully powered RCT.

Although the pilot trial is not designed to have statistical power for testing hypotheses, it will provide an estimate of the average and variability in the primary outcome variables, such as blood pressure, glucose, and lipid levels. These estimates of effect size would then help design the study size for the future larger randomized clinical trial, which would be powered for testing the intervention at the conventional levels of alpha = 0.05 and 80–90% power.

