#### Primary outcomes

2.9.1

The primary outcomes of this trial are changes in key physiological parameters among patients with mild-to-moderate stroke. These include: Blood pressure, Blood glucose, Blood lipid levels. Measurements will be collected at baseline, discharge, the end of the 3-month intervention, and at 3, 6, and 9 months post-intervention. These indicators constitute the primary endpoints as they represent the main clinical effects targeted by the AI-HEALS intervention.

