#### Exploratory outcomes

2.9.3

Exploratory outcomes reflect additional clinical, behavioral, and process-related indicators. These include Physiological monitoring indicators: level of consciousness, respiratory rate, heart rate and rhythm, height, weight, waist circumference, body mass index (BMI). Healthcare utilization indicators: 30-day hospital readmission and duration of hospital stay. Process indicators: recruitment and attrition rates, reasons for withdrawal, and differential characteristics between participants who discontinue the study and those who complete it.

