Measures of system use (e.g., numbers of questions) will be summarized descriptively and may be included as covariates in exploratory analyses to better understand adherence patterns; these analyses will be considered hypothesis-generating rather than confirmatory. All statistical tests will be two-tailed with a significance level of 0.05. Data analyses will be performed using IBM SPSS Statistics (version 24.0; SPSS Inc., Chicago, IL, United States) and Stata (version 14.0; StataCorp, College Station, TX, United States).

At 3, 6, and 9 months following the completion of the intervention, this study will conduct structured interviews to assess participants’ perception of the intervention as attractive, acceptable, easy to use, and satisfactory as a whole. These interviews will attempt to identify, in depth, the most prominent determinants of behavior change and engagement. Each interview should be approximately 30 min long to conduct and may be conducted over the telephone or face-to-face. Participant recruitment will take into account socio-demographic variables like residence, gender, age, education level, as well as stroke severity, to attain diverse representation. Content of interview will include participants’ own experience of the intervention, suggestions for improvement of AI-HEALS system, motivation to pursue self-management activities, as well as challenges that develop in the process. To attain richness as well as data breadth, interviews should be continued until thematic saturation has been achieved. All interviews should be audio-recorded, transcribed verbatim, as well as de-identification carried out on them. Data analysis should make use of the Theoretical Domains Framework (TDF) on NVivo 12 (Version 12, QSR International, Doncaster, Australia). Lastly, qualitative findings would be integrated with quantitative data to attain a richer understanding of the impact of the intervention as well as long-term effects on participants’ health behavior as well as outcomes.

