The AI-HEALS has the aim of enhancing stroke care through the use of artificial intelligence and mobile health technologies. It offers personalized health education as well as behavior change support to stroke patients and their families. Key system functions include knowledge-based question-answering services, health indicator monitoring, and personalized educational content and support tailored to the specific needs of stroke patients and their caregivers. Additionally, AI-HEALS enables care providers to monitor clients’ real-time system usage via a backend platform, facilitating the assessment of educational needs and the utilization of the intervention plan, thereby ensuring its effective implementation. Pilot studies have already indicated the tremendous promise of mobile technologies of health to deliver improved clinical outcomes when applied to stroke care. Through the support of large language models, AI-HEALS still promises to attain improved control of symptomatic improvement as well as improved recovery among patients that have mild to moderate stroke.

Based on this, this project will conduct a single-blind RCT to evaluate the effectiveness and acceptability of the AI-HEALS system in patients with mild to moderate stroke. Its primary objective will be to establish changes to patients’ blood glucose, blood pressure, and lipid profiles as a consequence of the intervention. Its secondary endpoints will include changes to perceived risk of stroke recurrence, physical health indicators such as hospital readmission rates, BMI, psychological and behavioral endpoints related to self-management of health plans, family involvement, as well as quality of life broadly. These endpoints will be examined using a combination of quantitative methods, such as standardized questionnaires and physiological measurements, and qualitative interviews. Due to the complex behavior and medical conditions involved when experiencing mild to moderate stroke, AI-HEALS has significant potentials of enhancing patient engagement as well as enhancing treatment guideline adherence.

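### The sample size is justified by a feasibility objective, but the declared primary endpoints are physiological effects tested at 0.05 and feasibility is ranked as exploratory

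*Protocol article*

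**What the plan says.** Section 2.4 (Sample size) gives the primary objective as whether the programme is "feasible, acceptable, and easily implementable, as opposed to determining the efficacy of the program". It takes 25 per group from a pilot-study recommendation, inflates this to 30 for 20% dropout, and adds: "Although the pilot trial is not designed to have statistical power for testing hypotheses". The size is expected to give "reliable estimates of feasibility parameters and preliminary effect size estimates", and the effect estimates are to help size a later trial, which would be "powered for testing the intervention at the conventional levels of alpha = 0.05".

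Other sections set a different aim:

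- The Abstract and section 2.9.1 name blood pressure, blood glucose and blood lipids as primary. Section 2.9.1 says: "These indicators constitute the primary endpoints as they represent the main clinical effects targeted by the AI-HEALS intervention".
- The Discussion says of the same three measures: "Its primary objective will be to establish changes to" them as a result of the intervention.
- Section 2.5 says that patients are enrolled to evaluate efficacy.
- Section 2.9.3 places feasibility among the exploratory outcomes: "Process indicators: recruitment and attrition rates, reasons for withdrawal".
- Section 2.11 states: "All statistical tests will be two-tailed with a significance level of 0.05". It places acceptability in interviews at 3, 6 and 9 months after the intervention ends. Acceptability appears in none of the outcome tiers in section 2.9.

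**The concern.** The primary objective decides what a trial may conclude. Here the size rests on one objective and the outcome hierarchy on another, and section 2.4 explicitly rules out the second. Two consequences follow.

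First, a set of physiological endpoints labelled primary, without a named lead and without planned power, will be tested at 0.05. A single nominally significant result could be read as effectiveness, and a null result as failure. Neither reading would be sound.

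Second, the quantities the sample was chosen to estimate have no primary outcome, and acceptability is first asked three months after use of the system has ended. Section 2.4 also carries this trial's observed effects into the planning of the next trial, where their imprecision would be inherited.

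**Working it through.** **1. The plan's own figure.** 25 × 1.2 = 30 per group, 60 in total, as stated. With 20% dropout, 60 × 0.8 = 48 remain, or 24 per arm. I therefore use 24–25 evaluable per arm.

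**2. Number of primary variables and visits.** Section 2.9.1 names three domains. Section 2.10.2 measures them as systolic and diastolic pressure (2), HbA1c (1), and total cholesterol, triglycerides, HDL-C and LDL-C (4), so 7 variables. Section 2.9.1 has five post-baseline visits: discharge, end of intervention, and 3, 6 and 9 months later. That is 7 × 5 = 35 possible contrasts. Seven is inferred from the measurement section; the outcome section does not state it.

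**3. Chance of at least one false-positive primary result**, each test at 0.05:
- 7 independent tests: 1 − 0.95^7 = 30%.
- 7 tests with an assumed common correlation of 0.2 to 0.5 (simulation): 29% down to 23%.
- 35 independent tests: 1 − 0.95^35 = 83%. The document does not plan 35 tests, so this is an upper bound only.

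**4. Power for one variable**, two-sided 0.05. The documents give no effect size or SD, so differences of 0.3 and 0.5 SD are assumed.
- Unadjusted t-test at one visit, 24/25 per arm: 17%/18% at 0.3 SD and 40%/41% at 0.5 SD. The difference detectable with 80% power is 0.83/0.81 SD.
- With baseline as a covariate, the residual SD is √(1 − r²) times the raw SD. At an assumed r of 0.5 this is 0.866, so 0.5 SD acts as 0.577 SD and power is 50–52%. At r = 0.7 it is 0.714, so 0.5 SD acts as 0.700 SD and power is 66–68%.

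**5. Precision of the effect estimate.** The 95% half-width is t × √(2/n). At 24 per arm it is 2.013 × √(2/24) = 0.58 SD; at 25 it is 0.57 SD. If the truth is 0.3 SD, estimates from about −0.3 to 0.9 SD are unremarkable. At 80% power, a next trial sized on an observed 0.87 SD would need about 22 per arm; sized on 0.3 SD it would need about 176.

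**6. What 60 patients can do.** Retention of 48/60 (80%) has a 95% Wilson interval of about 68% to 88%. An SD estimated on 46 degrees of freedom has a one-sided 80% upper limit of √(46/χ²₀.₂₀,₄₆) = 1.10 times the observed value. Both are useful planning quantities.

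**The case against.** Section 2.4 openly disclaims power, calls the effect sizes preliminary, and says only that they would help to plan the next trial. Section 2.11 names mixed models and no visit-by-visit tests for the physiological outcomes, and ties those models to the main trial, which may mean the future one. Feasibility is not neglected: recruitment, attrition and reasons for withdrawal are collected (2.9.3), system use is monitored weekly (2.8), and both are to be summarised descriptively (2.11). A lead variable may be named in a fuller document that is not shown.

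Much of this stands, and it rules out several stronger readings that a reader might infer:

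- That neither question gets a valid answer. An exploratory label does not invalidate a descriptive rate.
- That a false-positive primary result is probable. That needs the 35 visit-wise tests; one test per variable gives 23–30%.
- That the low power figures describe the planned analysis. They are for an unadjusted comparison at one visit, and a model using baseline would do better.
- That the Introduction also states a contrary primary objective. It lists three unranked objectives, and its physiological list has body weight in place of lipids.
- That HbA1c at discharge cannot respond. Section 2.10.2 says that it averages the preceding 2–3 months, so a short-interval change is attenuated, not impossible.

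None of this removes the contradiction. The article itself fixes the hierarchy, and fixes it against its own sample-size rationale. The ambiguity over the main trial does not help, because no other model for the primary outcomes is given.

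**Conclusion.** The point holds as an internal contradiction. Section 2.4 conflicts with the Abstract and sections 2.5, 2.9.1, 2.9.3 and 5 on what the trial is primarily for.

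If the physiological endpoints stay primary as written, the false-positive risk across seven variables is about 23–30%. Power for a 0.5 SD effect is about 40% unadjusted and perhaps 50–68% with baseline adjustment. The observed standardised effect carries an error of about ±0.58 SD unadjusted, which makes it a poor basis for sizing the next trial.

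These figures rest on 24–25 evaluable per arm, one test per variable, and assumed effect sizes and correlations that the documents do not supply. The contradiction depends on none of them.

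**What to change.** 1. In 2.9.1, make the feasibility measures already collected the primary outcomes: recruitment, retention at the end of the intervention, and AI-HEALS use. Ask acceptability at the existing end-of-intervention visit.
2. Reclassify blood pressure, HbA1c and lipids as preliminary clinical outcomes, reported as between-group differences with 95% confidence intervals and no effectiveness claim. If one test is kept, name one variable at the end of the 3-month intervention.
3. Give HbA1c at discharge no weight as an effect measure.
4. In 2.4, carry forward SDs (with an upper confidence limit, about 1.10 times the observed SD) and retention. Set the next trial's target difference on clinical importance, not on the observed effect.
5. Align the Abstract, the Introduction's objectives, sections 2.4, 2.5, 2.9.1, 2.9.3 and 2.11, the Discussion and the registry entry.

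The cost is more than rewording. Section 3 routes protocol changes through the Steering Committee, the Ethics Committee and the Research Administration Office, with a registry update, and section 2.3 dates recruitment from February 2025. One short acceptability form is added and no further patients are needed. The trial gives up an effectiveness claim that it cannot support.

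### Recruiting 60 at the stated 20% dropout leaves 48 completers (24 per group), short of the plan's own minimum of 50 (25 per group)

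*Protocol article*

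**What the plan says.** Section 2.4 (Sample size) of the protocol article bases the sample size on a published recommendation for pilot studies, not on a power calculation. It gives three figures in succession:

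- The target: "the minimum number of participants for our study would be 50, consisting of 25 per group".
- The loss allowance, an expected dropout of 20%, and the recruitment figure that follows from it: "Taking into consideration the expected dropout of 20%, the minimum number of people to recruit would be 60, 30 for each group".

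Section 2.2 (Randomization and blinding) fixes equal allocation: "For allocation, it would use the 1:1 allocation ratio". Section 2.4 adds that "the pilot trial is not designed to have statistical power for testing hypotheses". No other section gives a different dropout rate, target or inflation formula.

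**The concern.** The allowance for dropout is there so that the target is still met after the expected losses. Here it does not do so: taking 20% off the recruitment figure gives a number below the target it was meant to protect, in total and in each group.

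This target is the only justification the article gives for the size of the trial. The article relies on it for usable estimates of the feasibility parameters and for the preliminary effect sizes that will be used to plan a larger trial. As printed, the minimum to recruit does not deliver the minimum required, and a reader who checks the sentence will find that it contradicts itself.

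**Working it through.** **Inputs**, from sections 2.4 and 2.2:

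- Required number: 50 in total, 25 per group.
- Expected dropout: d = 0.20.
- Stated number to recruit: 60 in total, 30 per group.
- Allocation: 1:1.

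**Reproducing the stated figure.** Multiplying the target by (1 + d) gives 50 × 1.2 = 60 and 25 × 1.2 = 30, exactly the published figures. Dividing by (1 − d) does not give 60. The article states no formula, so the multiplication is an inference, though it fits exactly.

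**Expected completers from the stated figure.**

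- Total: 60 × (1 − 0.20) = 48, which is 2 below 50.
- Per group: 30 × (1 − 0.20) = 24, which is 1 below 25.

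**Number needed to keep the target.** The formula is N/(1 − d).

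- Total: 50/0.80 = 62.5, rounded up to 63.
- Per group: 25/0.80 = 31.25, rounded up to 32, so 64 in total with equal groups.
- Expected completers from 64: 64 × 0.80 = 51.2, or 25.6 per group.

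**Dropout that 60 can absorb.** 1 − 50/60 = 0.167, so 60 recruits keep 50 only if dropout is at most 16.7%.

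**Illustration of the spread.** This assumes that each participant drops out independently with probability 0.20; the independence is my assumption, not the article's.

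| Recruited | Expected completers | Chance of at least 50 in total | Chance that both groups reach 25 |
|---|---|---|---|
| 60 (30 per group) | 48 | 32% | 18% |
| 64 (32 per group) | 51.2 | 71% | 49% |

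The last column is the square of the one-group probability, 0.428 for 30 and 0.698 for 32. The 64 row is needed for a fair reading: even the correct inflation secures the target only on average, so chance variation accounts for much of the shortfall in the 60 row.

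**Effect on precision.** Going from 50 to 48 completers widens standard errors by √(50/48) = 1.021, about 2%. For a proportion of 50%, the 95% half-width 1.96 × √(0.25/n) moves from 13.9 to 14.1 percentage points.

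**The case against.** The strongest case on the other side accepts the arithmetic and argues that it hardly matters.

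- **The trial is a pilot with no power claim.** This is right. No alpha, power or effect size depends on the 50, and a 2% change in standard errors alters none of the stated objectives. It limits the importance of the point but does not make the sentence correct.
- **Intention-to-treat analysis, multiple imputation and mixed models (section 2.11) use participants with partial data.** Also right, and attrition and the reasons for withdrawal have all recruits as their denominator. Those who drop out therefore still contribute, and the corrected sentence should speak of completers, not evaluable participants. The inconsistency remains, because the plan itself adds recruits for dropout and so treats 50 as the number wanted after losses. If 50 meant participants randomised, no inflation would be needed.
- **Sixty is called a minimum, so more may be enrolled.** True, but a minimum that falls short under its own dropout assumption is the wrong minimum.
- **The cause is inferred.** This stands. The most one can say is that 60 is consistent with multiplying by 1.2. The contradiction does not depend on how 60 was reached.

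**Conclusion.** The concern holds. The stated minimum to recruit is inconsistent with the stated target and the stated dropout rate. The expected shortfall is 2 completers in total, 1 per group, and correct inflation needs 3 more recruits (63) or, with equal groups, 4 more (64).

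The conclusion rests only on the article's own three figures and on reading 50 as the number needed after dropout, which the plan's own inflation implies. The probabilities rest in addition on independent dropout and are secondary. This is a clear numerical error that should be corrected. Its practical effect is small, and it does not threaten the pilot's conduct or analysis.

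**What to change.** The preferred change keeps 60 and rewrites one sentence in section 2.4, for example: *Recruiting 60 participants (30 per group) is expected to give 48 completers (24 per group) at 20% dropout; the minimum of 50 is met if dropout is at most 16.7%.* This needs no extra participants and no change to design or analysis. The only cost is a slightly less favourable statement of the expected yield.

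If the sponsor wants 25 completers per group to be expected at 20% dropout, the sentence should give 64 recruits (32 per group), which costs 4 more participants.
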